### Sample size, power, and effect size

We present power calculations for the primary outcome HVL suppression at 3 months post randomization. The calculations assume an alpha level of 0.05 and that 300 participants are enrolled into the trial. The GRAIL trial was initially designed to be conducted in Russia, with our sample size justification derived from prior research conducted among the Russian population. Based on data from our previous study of Russian people with HIV and risky drinking [14], we expect 40% of control participants will have undetectable HVL at 3 months. Given this and assuming 15% loss to follow-up at 3 months (i.e., 255 evaluable subjects) the study will have 80% power to detect an absolute difference of 19% in the proportions with undetectable HVL at 3 months (i.e., 59% vs. 40% in the gabapentin and control arms, respectively) using a chi-square test with continuity correction. We anticipate larger effects may be observed in the GRAIL trial, which would result in even higher power. In the Russian study, among participants on ART who reduced alcohol consumption, approximately 76% had HVL suppression at the 3-month follow-up. If a similar proportion achieves HVL suppression in the gabapentin arm, the study would have > 99% power to detect this 36% difference between randomized groups (i.e., 76% vs. 40% in the gabapentin and control arms, respectively). The trial is adequately powered to detect differences between arms as small as 19%, which are still considered clinically meaningful.

### Missing data

Participants who meet eligibility criteria and agree to participate will be compared with participants who were determined to be eligible but declined enrollment on data captured during eligibility assessment. Missing data patterns will be evaluated including the frequency and percentage of participants missing for each variable and the distribution of the number of variables missing for participants. In addition, data collected to the point of loss to follow-up will be compared to the data of those who complete the study to examine missing data mechanisms. The proposed study has accounted for a 15% random non-informative loss to follow-up and will still have sufficient power with this potential loss in size. It may be reasonable to assume that data are missing at random, albeit not completely. If this is the case, multiple model-based imputation methods will be applied to account for the missing data, if needed. We will also consider the use of pattern mixture models, which is applicable when the data are not missing at random. Pattern mixture models involve classifying subjects based on their longitudinal missing data patterns and assessing whether there appears to be an interaction between a randomized group and missing data pattern.

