### Randomization

Randomization is conducted and monitored by the data management team. Participants are randomized in a 1:1 ratio using permuted blocks with a fixed block size of two, stratified by: i) self-reported alcohol use severity score (Alcohol Use Disorders Test (AUDIT) > 20 vs. ≤ 20) and ii) clinic site. We assumed participants with severe alcohol use may be less likely to reach HVL suppression over the study period than those who are drinking less alcohol.

Randomized group allocations are concealed using scratch-off cards. Before recruitment, the study pharmacist received a randomization list containing sequential card numbers for ordering and a unique 5-digit code (randomization result) indicating the medication assigned arm (gabapentin and placebo). Each scratch-off card displays only the card number, while the randomization code remains hidden until the participant scratches off the covering. The AUDIT score stratum is distinguished by the color of the scratch card (i.e., yellow for AUDIT > 20 and green for AUDIT ≤ 20).

During randomization, RAs present participants with the top four sequential scratch-off cards from the appropriate AUDIT pile. Participants select one card, scratch it off, and reveal the randomization result. Based on the result, the RA provides the corresponding medication package labeled with that unique randomization number. The next sequential card is then added to the pile, ensuring that four cards are consistently available for subsequent participants.

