### Analytic methods

The study uses an intention-to-treat analysis that includes all participants according to their randomized assignment. Descriptive statistics are calculated for variables at baseline and each follow-up time to assess whether there appear to be any differences across treatment arms. Spearman correlation analyses are performed to identify pairs of variables that may be collinear. In addition, the variance inflation factor is assessed to detect possible collinearity.

The primary outcome for this study is undetectable HVL (< 200 copies/ml) at 3 months. The primary analysis uses multivariable logistic regression analyses to control for the randomization stratification factors to improve efficiency (i.e., AUDIT > 20, clinic site). If any baseline factors appear to differ by randomized group, additional sensitivity analyses will be conducted controlling for these factors to assess for potential confounding. Other binary outcomes (e.g., heavy alcohol consumption [defined as PEth ≥ 50 ng/mL], adherence to ART [defined as taking ≥ 80% of prescribed medication via Visual Analog Scale], engagement in HIV care [defined as ≥ 1 HIV visit in the past 3 months]) will be analyzed using the same approach. Number of heavy drinking days (assessed using the Timeline Followback [TLFB] method) in the past month will be analyzed using negative binominal regression, to account for overdispersion in the data. Percentage of ART pills taken (assessed by self-report), a continuous outcome, will be analyzed using multiple linear regression if the data are normally distributed. However, if the distribution is skewed, transformations of the data will be performed (e.g., log transformation). If an appropriate transformation is not identified, a median regression model will be used. A secondary analysis will be conducted using a per protocol approach that includes only those participants who were adherent to their assigned intervention (i.e., defined as taking at least 80% of the assigned medication), as determined by self-report (i.e., Visual Analog Scale).

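### The arm-by-missing-pattern interaction, the only form in which the plan describes a not-missing-at-random analysis, does not address participants lost before the month-3 primary outcome

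*Protocol article*

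**What the plan says.** All references are to the protocol article; the SAP is not shown.

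- **Missing data.** Loss is planned for as ignorable: "The proposed study has accounted for a 15% random non-informative loss to follow-up". The section then plans a comparison of those lost with those who complete. Multiple imputation under missing at random (MAR) follows, to be used only if needed. Pattern mixture models are to be considered for data not missing at random (MNAR), with this description: "Pattern mixture models involve classifying subjects based on their longitudinal missing data patterns and assessing whether there appears to be an interaction". The interaction meant is between randomised group and missing-data pattern.
- **Analytic methods.** The primary analysis is a logistic regression of HVL below 200 copies/ml at month 3, adjusted for the stratification factors. The analysis set is intention-to-treat: "The study uses an intention-to-treat analysis that includes all participants according to their randomized assignment". Models using months 3, 6 and 12 together are exploratory.
- **Laboratory testing and results; Table 1.** Follow-up HVL is measured at 3, 6 and 12 months. A detectable HVL is an entry criterion.
- **Sample size, power, and effect size.** "we expect 40% of control participants will have undetectable HVL at 3 months", and "the study will have 80% power to detect an absolute difference of 19% in the proportions with undetectable HVL at 3 months", "assuming 15% loss to follow-up at 3 months (i.e., 255 evaluable subjects").

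**The concern.** A pattern mixture model handles MNAR data by making an explicit assumption about the outcome in patterns where it was not observed. A test for an arm-by-pattern interaction makes no such assumption. It asks whether the arm effect differs between patterns in which the outcome was seen.

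For this primary outcome that leaves a hole. Participants who miss month 3 have no month-3 outcome. No earlier follow-up HVL exists, and suppression status at entry is the same for all. The month-3 arm effect in that pattern cannot be estimated from the data without an outside assumption. What remains is a contrast among people who do have a month-3 value, for example completers against those who drop out later. That is a check of heterogeneity and yields no MNAR-adjusted estimate of the primary effect.

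Informative loss is plausible here. Participants and recruitment says that the entry criteria are meant to select people who are probably not adhering to ART. The Intervention section foresees dose reductions for side effects, which could make loss differ by arm. A null interaction might be reported as evidence that missingness does not matter, although the relevant question had not been examined.

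**Working it through.** **Inputs from the article.** 300 randomised and alpha 0.05 ("The calculations assume an alpha level of 0.05 and that 300 participants are enrolled into the trial"); 1:1 allocation ("Participants are randomized in a 1:1 ratio using permuted blocks with a fixed block size of two"); 15% loss at month 3; 59% vs 40%; chi-square test with continuity correction. Two-sided testing is assumed, since the article does not state it.

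**Assumptions not in the article.** The split of the 45 losses by arm, and the outcomes of those lost. Ranges are shown.

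**1. The plan's own figure.** 300 × 0.85 = 255. Exact power of the continuity-corrected test with 127 and 128 evaluable is 82.3% at 59% vs 40%, and 77.7% at 58% vs 40%. So 19 points is the smallest whole-point difference with at least 80% power. The stated figure reproduces as a detectable difference rounded up.

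**2. What the interaction can use.**

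| HVL availability | Month-3 outcome | Month-3 arm effect estimable in this pattern? |
|---|---|---|
| Seen at 3, 6 and 12 months | observed | yes |
| Seen at 3, lost later | observed | yes |
| Missed 3, seen at 6 or 12 | missing | no; later values inform only a longitudinal model |
| No follow-up HVL | missing | no |

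The last two rows hold all the missing primary outcomes, and the interaction has no month-3 estimate in either.

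**3. Size, equal 15% loss per arm.** The difference over all 300 is 0.85 × 0.19 + 0.15 × (g − c), where g and c are the suppression proportions among missing gabapentin and missing control participants.

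- Missing = not suppressed in both arms (g = c = 0): 0.85 × 59% = 50.15% vs 0.85 × 40% = 34.0%, a difference of 16.15 points (16.2 rounded). Exact continuity-corrected power with 150 per arm is 78.8%.
- All-or-nothing bounds: 16.15 ± 15 gives +1.15 and +31.15 points.
- A difference of exactly zero needs c − g = 0.1615 / 0.15 = 1.08, which is impossible because a gap between two proportions cannot exceed 1.

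**4. In whole numbers.** Take 75/127 (59.1%) vs 51/128 (39.8%) observed, with 23 gabapentin and 22 control participants missing. The p-values are from the continuity-corrected chi-square test; on the observed data alone, p = 0.003.

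| Assumption for the missing | Gabapentin | Control | Difference (points) | p |
|---|---|---|---|---|
| None suppressed | 75/150 | 51/150 | 16.0 | 0.007 |
| About 40% suppressed in both arms | 84/150 | 60/150 | 16.0 | 0.008 |
| Gabapentin 0/23, control 6/22 | 75/150 | 57/150 | 12.0 | 0.048 |
| Gabapentin 0/23, control 7/22 | 75/150 | 58/150 | 11.3 | 0.063 |
| Gabapentin 0/23, control 22/22 | 75/150 | 73/150 | 1.3 | 0.91 |

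With no missing gabapentin participant suppressed, significance is lost at 7 of 22 missing controls suppressed, a gap of about 32 points.

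**5. Unequal loss, missing = not suppressed.**

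- 30 lost on gabapentin, 15 on control: 0.59 × 120 = 70.8, about 71; 0.40 × 135 = 54. So 71/150 vs 54/150, 11.3 points, p = 0.06.
- 15 on gabapentin, 30 on control: 0.59 × 135 = 79.65, about 80; 0.40 × 120 = 48. So 80/150 vs 48/150, 21.3 points, p = 0.0003.

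**The case against.** The strongest reply is that the article condenses a fuller protocol. The MNAR method is only to be considered, and identifying restrictions, delta values and imputation predictors normally belong in the SAP. Pattern mixture modelling is a sound framework, and nothing in the text forbids adding an assumption for those lost. This stands in part: the absence of delta values is no fault. But the article does say what its MNAR method consists of, and a SAP that carries out that description would inherit the gap. The multiple imputation named beside it assumes MAR, so it cannot serve as the MNAR check.

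A reader might infer more than the documents support:

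- **That the trial has no usable sensitivity analysis.** Multiple imputation and pattern mixture models are both named and can be made usable. The check-ins at weeks 1, 2, 3, 4, 6, 8 and 10 supply adherence and symptom data that strengthen MAR imputation.
- **That pattern mixture models are uninformative about HVL here.** People who miss month 3 and return at 6 or 12 months contribute to the exploratory longitudinal models. The gap concerns the month-3 effect as the interaction is described.
- **That 15% loss could wipe out the 19-point effect.** Under equal loss about 1 point remains even at the extreme, and if missing counts as not suppressed in both arms, 16 points remain.
- **That 255 evaluable contradicts an intention-to-treat analysis of 300.** Basing power on expected completers is ordinary planning, and imputation can bring everyone into the analysis. Non-informative loss for planning and MAR for analysis can both describe ignorable missingness.

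**Conclusion.** The point holds for the month-3 primary outcome. The MNAR method, as described, compares only participants with an observed month-3 value, so it cannot detect or correct informative loss before that visit.

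The consequence is moderate. On the plan's own figures, the result is fairly robust to balanced loss: significance goes only once suppression among missing controls exceeds that among missing gabapentin participants by roughly 32 points. It is more sensitive to unequal loss: a 30/15 split with missing counted as not suppressed cuts the effect to about 11 points and loses significance.

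These sizes rest on 59% vs 40% among those observed, 45 losses in total, and assumed splits and outcomes for the missing. The documents give no figure for how suppression relates to loss, so no scenario here is a forecast. The change is worth making because it replaces a stated method that does not fit the primary endpoint, at little cost.

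**What to change.** For the month-3 endpoint, replace the interaction check in Missing data with a pre-specified, assumption-based sensitivity analysis:

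1. Multiple imputation with arm-specific delta shifts away from MAR, shown as a tipping-point display over a stated range. Predictors: arm, stratification factors, baseline HVL where available, CD4 count, adherence and symptom data from the medication check-ins, and HVL at 6 and 12 months.
2. One further row analysing all 300 with missing counted as not suppressed. State beside it that this is itself an untestable assumption and is sensitive to loss that differs by arm, and report loss by arm next to it.

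The first item is a properly specified pattern mixture model, so the plan's chosen framework is kept. The interaction can stay as a description of heterogeneity in the longitudinal models. Fix the wording before unblinding; recruitment is expected to run to May 2026, so there should be time.

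Cost: revised SAP wording, a few extra tables, and possibly a smaller effect in the sensitivity rows. The row counting missing as not suppressed is affordable, at 78.8% power under equal loss against 82.3% for the planned 255 evaluable, but it falls to about 47% under the 30/15 split (47.2% vs 36.0%, 150 per arm).

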### Protection of study data

All study data are captured electronically on computers via a secure, web-based data capture system. The study data are located on a secure server within the Boston University Medical Center domain. Identifiers needed to track participants are kept separate from research data.

### Data safety monitoring board (DSMB)

To ensure the safety of the participants and the validity and integrity of the data, an external DSMB was established to assume oversight of the study. The DSMB operates independently of the study sponsor and study investigators and its members have no competing interests that could affect their objectivity in monitoring the safety and integrity of the study. The Board meets every 6 months and is charged with evaluating the quality of trial administration, monitoring safety issues, and providing guidance on scientific, methodological, and ethical issues. Specifically, the Board reviews investigators’ plans and processes for identifying individual or patterns of adverse events and reviews accumulating safety data. They may use results from an interim analysis to recommend that the study proceed as planned, be temporarily suspended, or be terminated. The DSMB charter is available as Additional File 2.

### Auditing

The research team has employed a Study Monitor to conduct monitoring visits at study recruitment sites and research office. These typically occur annually in order to review study documents, and collaborate with the research team to ensure compliance with protocols and regulations. The study monitor provides input without influence from investigators or sponsor.

### Participant graduation, withdrawal, and disenrollment

Participant disenrollment can occur at any time during the study upon a participant’s request to withdraw from study participation. Graduation for participants occurs after all procedures for the 12-month follow-up visit are complete or when a participant is withdrawn or terminated from the study. At their final study visit, participants receive a graduation certificate in appreciation of their contribution to the research.

### Dissemination plans

De-identified trial data are uploaded into the NIAAA Data Archive biannually. Study results will be submitted for publication in peer-reviewed journals relevant to the research topic. Abstracts will be submitted to national and international conferences relevant to the field.

## Discussion

The GRAIL study seeks to establish whether gabapentin can achieve HVL suppression among PWH with risky drinking. The study is being conducted in a setting of high HIV prevalence with unmet needs for treatment and prevention of alcohol use. If shown to be effective, this highly generalizable pragmatic approach, with the potential of rapid deployment of gabapentin due to its affordability and widespread availability, can be added to the HIV prevention toolkit and implemented within existing medical infrastructure.

### Trial status

The study was initially approved by the BUMC IRB on August 13, 2022 (version 1.1). The current version was approved on July 22, 2024 (version 1.6). Recruitment started on November 20, 2023 and is expected to complete in May 2026.

## Figures and Tables

**Figure 1 F1:**
[figure not shown]
GRAIL study design

**Figure 2 F2:**
[figure not shown]
Schedule of enrollment, intervention, and assessments (SPIRIT figure)

**Table 1 T1:** GRAIL eligibility criteria

**Inclusion Criteria**
18 years or older
Having an HIV diagnosis for at least 6 months (assessed via medical charts)
Current (within 2 months) detectable HIV viral load at least 6 months after HIV diagnosis (assessed via medical charts or study test)
Positive Ethyl Glucuronide (EtG) urine test (300 ng/ml cutoff)
Able and willing to comply with all study protocols and procedures
Living within 2 hours travel time of the study site
**Exclusion Criteria**
Not fluent in English or Runyankole
Cognitive impairment resulting in inability to provide informed consent based on research assistant assessment
Pregnancy, planning to become pregnant in next 3 months, or breast feeding (pregnancy assessed via study test)
Taking gabapentin/pregabalin in past 30 days (self-report)
Taking any medication for alcohol use disorder (self-report)
Known hypersensitivity to gabapentin (self-report)
Enrolled in another HIV research study seeking viral load suppression (self-report)
Unstable psychiatric illness (i.e., answered yes to any of the following: past three month active hallucinations; mental health symptoms prompting a visit to the ED or hospital; mental health medication changes due to worsening symptoms; presence of suicidal ideations)

**Table 2 T2:** GRAIL medication dosing schedule

Week 1: 1 capsule per day; 7 capsules total							
	Day 1	Day 2	Day 3	Day 4	Day 5	Day 6	Day 7
Morning	1 capsule	1 capsule	1 capsule	1 capsule	1 capsule	1 capsule	1 capsule
Afternoon							
Evening							
Total	1	1	1	1	1	1	1
Week 2: 3 capsule per day; 21 capsules total							
	Day 1	Day 2	Day 3	Day 4	Day 5	Day 6	Day 7
Morning	1 capsule	1 capsule	1 capsule	1 capsule	1 capsule	1 capsule	1 capsule
Afternoon	1 capsule	1 capsule	1 capsule	1 capsule	1 capsule	1 capsule	1 capsule
Evening	1 capsule	1 capsule	1 capsule	1 capsule	1 capsule	1 capsule	1 capsule
Total	3	3	3	3	3	3	3
Week 3, 4, 5, 6, 7, 8, 9, 10, 11: 6 capsule per day; 42 capsules total							
	Day 1	Day 2	Day 3	Day 4	Day 5	Day 6	Day 7
Morning	2 capsules	2 capsules	2 capsules	2 capsules	2 capsules	2 capsules	2 capsules
Afternoon	2 capsules	2 capsules	2 capsules	2 capsules	2 capsules	2 capsules	2 capsules
Evening	2 capsules	2 capsules	2 capsules	2 capsules	2 capsules	2 capsules	2 capsules
Total	6	6	6	6	6	6	6
Week 12: 33 capsules total							
	Day 1	Day 2	Day 3	Day 4	Day 5	Day 6	Day 7
Morning	2 capsules	2 capsules	2 capsules	2 capsules	1 capsule	1 capsule	1 capsule
Afternoon	2 capsules	2 capsules	2 capsules	2 capsules	1 capsule	1 capsule	1 capsule
Evening	2 capsules	2 capsules	2 capsules	2 capsules	1 capsule	1 capsule	1 capsule
Total	6	6	6	6	3	3	3

## Data Availability

Data and materials will be provided upon reasonable requests to the corresponding author.

## Abbreviations

AE: Adverse event
ART: Antiretroviral therapy
AUDIT: Alcohol Use Disorders Identification Test
AUDIT-C: Alcohol Use Disorders Identification Test- Concise
BPI-SF: Brief Pain Inventory- Short Form
CD4: Cluster of differentiation 4
CESD-10: Center of Epidemiologic Studies Depression Scale, 10-item version
DSMB: Data Safety Monitoring Board
DSM-5: Diagnostic and Statistical Manual of Mental Disorders
EtG: Urine ethyl glucuronide test
GAD-7: Generalized Anxiety Disorder-7
GEE: Generalized estimating equations
HVL: HIV viral load
IRB: Institutional Review Board
ISS: Immune Suppression Syndrome Clinic
MUST: Mbarara University of Science and Technology
NIAAA: National Institute on Alcohol Abuse and Alcoholism
PEth: Phosphatidylethanol
PWH: People with HIV
RA: Research assistant
REDCap: Research Electronic Data Capture
SAE: Serious adverse event
TLFB: Timeline Followback
UGX: Ugandan Shilling
USD: United States dollar
